### Blinding

Because of the nature of acupuncture treatment, it is not possible to adopt a double-blinded study design. Therefore, we will adopt an outcome-assessor-blinded trial procedure. During the course of this clinical trial, the assessor will not contact any participant other than at the time of assessment. Furthermore, assessor unblinding will not be permitted under any circumstance. For preventing selection, performance, and attrition biases due to unblinded participants and practitioners, this study will only involve individuals without conflicts of interest or preconceived positions. All practitioners will receive training in clinical trials before participation. A statistician, who was not involved in the design or execution of the clinical trial, will analyze the final data.

### Interventions

Participants will receive acupuncture treatment once per day, 3 days/week (excluding Saturdays and Sundays) for 8 weeks. The treatment will be administered by Korean medicine doctors with 6 years of formal university training in Korean medicine and a license to administer treatment. To ensure strict adherence to the study protocol, the doctors will receive training together and use the same techniques (Table 1).

**Table 1 Tab1:** Revised Standards for Reporting Intervention in Clinical Trials of Acupuncture (STRICTA)

Item	Item criteria	Description
1. Acupuncture rationale	1a) Style of acupuncture	Korean medicine therapy
	1b) Reasoning for treatment provided—based on historical context, literature sources, and/or consensus methods, with references where appropriate	• Discussion among four doctors that practice Korean medicine (consensus) • Textbook of acupuncture and moxibustion medicine • Relevant articles [9, 17–22] Selection of treatment regions based on textbooks, related papers, and expert discussions
	1c) Extent to which treatment varied	Standardized treatment
2. Details of needling	2a) Number of needle insertions per subject per session (mean and range where relevant)	8 or 10
	2b) Names (or location if no standard name) of points used (unilateral/bilateral)	Baihui (GV20), Sishencong (EX-HN1), Fengchi (GB20), Shenting (GV24), Taixi (KI3)
	2c) Depth of insertion, based on a specified unit of measurement or on a particular tissue level	Needles will be inserted into the acupoints subgaleally along the scalp at an angle of 15–30°. GB20 will be punctured 17–30 mm in the direction toward the nose tip. GV24, the anterior EX-HN1, and GV20 will be punctured forward, and the left, right, and posterior EX-HN1 toward GV20. The depth of insertion will be 9–24 mm depending on the location of the needle. KI3 will be punctured bilaterally, vertically to a depth of 9–15 mm [9, 23]
	2d) Responses sought	No de qi or muscle twitching—only sensation due to needle insertion
	2e) Needle stimulation	None or electrical stimulation
	2f) Needle retention time	30 min per session or 20 min per session
	2 g) Needle type	Sterile, stainless, disposable acupuncture needles (size 0.25 mm × 30 mm, product no. A 84010.02; Dong Bang Acupuncture, Inc., Boryeong, Republic of Korea)
3. Treatment regimen	3a) Number of treatment sessions	24
	3b) Frequency and duration of treatment sessions	3 days/week for 8 weeks, 30 min per session or 20 min per session
4. Other treatment components	4a) Details of other interventions administered to the acupuncture group	None
	4b) Setting and context of treatment—including instructions to practitioners—as well as information and explanations given to patients	Practitioner–patient conversation about the context of the treatment, life habits, and daily life management
5. Practitioner background	5a) Description of participating acupuncturists	Korean medicine doctor with the following qualifications: 6 years of formal university training in Korean medicine and a license
6. Control or comparator interventions	6a) Rationale for the control or comparator in the context of the research question, with sources that justify the choice	[9]
	6b) Precise description of the control or comparator; details for items 1–3 with the use of sham acupuncture or any other type of acupuncture-like control	This study will investigate the optimal acupuncture treatment method for the treatment of mild cognitive impairment (MCI) through a comparison of the effects of different acupuncture treatment methods according to acupoint specificity, needle duration, and electrical stimulation in terms of an improvement in cognitive function in patients with MCI. There is no control or comparator

### BA group

BA treatment will be acupuncture administered at Baihui (GV20), Sishencong (EX-HN1), Fengchi (GB20), and Shenting (GV24) [9, 15]. Only sterile, stainless steel, disposable acupuncture needles (size 0.25 mm × 30 mm, product no. A84010.02; Dong Bang Acupuncture, Inc., Boryeong, Republic of Korea) with guide tubes will be used for treatment. With participants in the sitting position, needles will be subgaleally inserted at an angle of 15–30° along the scalp. GB20 will be punctured 17–30 mm in the direction of the tip of the nose. GV24, anterior EX-HN1, and GV20 will be punctured in the forward direction, while the left, right, and posterior EX-HN1 will be punctured in the direction of GV20. The depth of insertion will be 9–24 mm, depending on the location of the needle [23]. After insertion, the needles will be left in position for 30 min. Manual stimulation will not be used.

### AS group

The AS acupuncture treatment method will be the same as the BA treatment method except for additional acupuncture treatment at Taixi (KI3) [18–21], where acupuncture needles will be inserted bilaterally and vertically to a depth of 9–15 mm [23] for 30 min.

### ND group

The acupuncture treatment method for the ND group will be the same as that for the BA group, except that the needles will be retained for 20 min instead of 30 min [22].

### EA group

The acupuncture treatment method for the EA group will be the same as that for the BA group, except that it will involve electrical stimulation of the acupoints using an EA stimulator (CELLMAC PLUS, STN-330, product no. A16010.04; Stratek, Co., Ltd, Anyang, Republic of Korea). GV24and GV20, the left and right EX-HN1, the anterior and posterior EX-HN1, and the left and right GB20 will be subjected to EA under the following parameters: continuous waves; frequency, 3–15 Hz; and intensity, 2–4 mA [9].

During the clinical trial period, all participants will be allowed to continue their routine management regimens (including regular physical exercise), existing medications (such as those for hypertension, diabetes, or hyperlipidemia), and medications for maintaining and improving their health status. However, they will not be permitted to engage in other treatments (e.g., pharmacological treatment or cognitive rehabilitation) for ameliorating their MCI symptoms. All medical devices, including the acupuncture needles and EA stimulator, will be inspected by the investigators, who will record their findings in the management register.

### Outcome measurements

The scores for the ADAS-K-cog, MoCA-K, CES-D, K-ADL, K-IADL, and EQ-5D-5L scales will be recorded before treatment, at the end of treatment, and 12 weeks after treatment completion.

General cognitive performance will be evaluated using the ADAS-K-cog. The ADAS-cog is a quantitative instrument for evaluating comprehensive cognitive functions involving memory, language, praxis, and frontal lobe function [24]. It is also used for judging the efficacy of anti-dementia treatments [22, 25, 26]. The scale has been translated into Korean and validated [27]. This adapted scale includes tests for word recall, naming of objects and fingers, commands, constructional and ideational praxis, orientation, word recognition, spoken language and comprehension, word finding, and recall of test instructions. Higher scores indicate higher degrees of deficit [28].

The MoCA scale is a clinician-friendly, validated, brief instrument with high sensitivity and specificity for detecting MCI [29]. It has been translated into Korean and validated [30]. Subscales of this tool include tests for evaluating overall cognitive function, including visuospatial ability, executive function, attention–concentration–working memory, language, short-term memory recall, and orientation to time and place [30].

The CES-D scale is a short self-report scale designed to measure the current level of depressive symptomatology, including depressed mood, feelings of guilt and worthlessness, feelings of helplessness and hopelessness, psychomotor retardation, loss of appetite, and sleep disturbance. Patients are asked to rate each item using an ordinal 4-point Likert scale [31].

The K-ADL and K-IADL scales will be used for assessing physical function. The K-ADL scale was developed to assess basic activities of the elderly, including dressing, washing, bathing/showering, eating, getting out of bed/the bedroom, using the toilet, and controlling urination. The K-IADL scale is used for estimating more complex activities necessary for an independent daily life, including personal grooming, household chores, preparing meals, doing laundry, going out within a short distance, using transportation, shopping, managing money, making telephone calls, and taking medications [32]. Combining IADL and ADL items on the same scale provides an enhanced range and sensitivity of measurement [33].

The European Quality of Life Five Dimension (EQ-5D) scale is a generic instrument for assessing health-related quality of life, comprising five dimensions: mobility, self-care, usual activities, pain/discomfort, and anxiety/depression. Each dimension has three response categories, including no problems, some/moderate problems, or severe/extreme problems. The EQ-5D-5L, which will be used in this study, is a new version of the EQ-5D that includes five levels of severity in each of the existing five dimensions [34].

### Occurrence of adverse events

Adverse events (AEs) are undesirable and unintentional signs, symptoms, or diseases that appear during or after treatment in a clinical trial. Participants in this study will be required to voluntarily report any AEs. All AEs that occur during the trial will be documented. AEs that could occur in this study include skin irritation, bleeding, local hematoma, pallor, sweating or dizziness, fainting during acupuncture treatment, needle retention after treatment, continuous severe pain for more than 1 h after acupuncture treatment, or objective worsening of existing symptoms. The CRC will record all AEs in detail, including the time and date of occurrence, degree of severity, any measures related to treatment of the AE, and any potentially causal relationship between the trial and AE, as well as report all AEs to the PI and relevant IRB. In the case of SAEs, defined as those causing severe disability or malfunction, appropriate measures will be taken and the incident will be immediately reported to the PI and relevant IRB. If an AE is determined to occur because of the clinical trial, participants will notify the CRC and the PI and be compensated.

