### Hypothesis

The null hypothesis is that randomization of patients into four equal groups each receiving a different acupuncture protocol is not feasible and/or acupuncture is not safe for MCI patients and different acupuncture treatment methods will provide similar improvements in cognitive function in MCI patients.

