### Participant recruitment

Participants will be recruited at the DongShin University Gwangju Korean Medicine Hospital in the Republic of Korea. The study will be advertised through local newspapers, the Internet, and posters in communities and hospitals. Interested individuals will learn how to participate in this clinical trial through telephone calls or visits to our hospital. During visits to the clinical research center of DongShin University Gwangju Korean Medicine Hospital, the clinical research coordinator (CRC) will explain the study to the participants, who will be asked to voluntarily sign an informed consent form before participation. In order for the enrolled participant to be able to complete treatment and evaluation, the CRC will adjust the treatment and evaluation schedule of the enrolled participant to facilitate participation in this study. Every time the enrolled participant visits, the CRC will explain the next visit’s schedule; and the day before the visit, the CRC will remind the enrolled participant of the schedule by telephone. The CRC will continuously monitor the medical condition of enrolled participants to ensure adherence to the intervention protocols.

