### Inclusion criteria

Participants meeting all of the following criteria will be included in this trial: male or female aged 55–85 years; fulfillment of the Petersen diagnostic criteria for MCI [1] (i.e., subjective memory complaint, normal general cognitive function, objective memory impairment, not severe enough to interfere with ADL, and no dementia) with memory impairment for at least the 3 months preceding enrollment; score of 20–23 on the Korean version of the Mini-Mental State Examination (MMSE); score of 0–22 on the MoCA-K; sufficient language fluency to reliably complete all study assessments; and willingness to sign the informed consent form.

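### Voluntary report is the only stated way of finding adverse events in a memory-impaired sample, so AE counts may be too low, by an unknown amount

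*Protocol article*

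**What the plan says.** The section Occurrence of adverse events defines AEs as "undesirable and unintentional signs, symptoms, or diseases that appear during or after treatment in a clinical trial", so the period after treatment is in scope. It then gives the route by which they become known: "Participants in this study will be required to voluntarily report any AEs". The next sentence promises completeness: "All AEs that occur during the trial will be documented". The CRC is to record each AE in detail. The section lists events to expect. Some would be visible to staff, such as bleeding, pallor and fainting during treatment. Another is "continuous severe pain for more than 1 h after acupuncture treatment".

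Under Inclusion criteria, participants must meet diagnostic criteria that include objective memory impairment, "with memory impairment for at least the 3 months preceding enrollment". Under Hypothesis, the null includes the statement that "acupuncture is not safe for MCI patients".

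Under Participant recruitment, the coordinator is in regular touch with participants: "Every time the enrolled participant visits, the CRC will explain the next visit’s schedule". A reminder call follows on the day before each visit. The same section says that the coordinator monitors participants' medical condition, for the stated purpose of adherence.

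**The concern.** Spontaneous reporting asks the participant to remember an event, recognise that it matters and raise it without being asked. That suits poorly a sample chosen for impaired memory. The protocol prompts these participants about appointments but describes no prompt about AEs.

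The rule also conflicts with its surroundings. A report cannot be both required and voluntary, and a system of volunteered reports cannot by itself ensure that every AE is documented.

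Forgotten events lower the count. Because the null hypothesis includes lack of safety, a low count favours rejecting that part of it. With 32 participants, a few missed events could change the safety description.

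**Working it through.** **1. The plan's own figures.** Sample size: 4 groups × 8 = 32. Sessions: 3 per week × 8 weeks = 24. Last assessment: 8 + 12 = week 20. All three agree with the document. It states no AE rate and no reporting rate.

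**2. Contact over time.**
- Weeks 0 to 8: 24 sessions with a treating doctor, usually a few days apart, and a reminder call the day before each visit.
- Weeks 8 to 20: one assessment at the end, with its reminder call. Study design and setting and Outcome measurements mention nothing in between, and for the week-20 assessment they name only scale scores.
- Length of the second interval: 12 × 7 = 84 days out of 20 × 7 = 140 days; 84/140 = 60%.
- An event just after the end of treatment might therefore have to be recalled up to about 84 days later. This is the extreme case.

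**3. Who could notice the named events.**
- Staff at the session: bleeding, pallor, sweating, fainting during treatment. A hematoma or a needle left in place can also be seen in clinic.
- Participant (or family) only: pain lasting more than an hour after treatment, once the participant has gone home; any event that arises and resolves between sessions; any event that arises and resolves between week 8 and week 20.

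For the second group, the only stated route into the trial record is the participant's own report.

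**4. What a clean safety record could show.** If no event of a given type is recorded in n participants and every event is captured, the one-sided 95% upper limit for the risk is 1 − 0.05^(1/n).
- All participants: 1 − 0.05^(1/32) = 0.089, or 8.9%.
- One arm: 1 − 0.05^(1/8) = 0.312, or 31.2%.

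These limits reflect the pilot's size, not its AE collection. If only a fraction s of affected participants have the event recorded, the limit for the true risk becomes approximately the same figure divided by s. For any s below 1 it is higher, so 8.9% is the best case. The document gives no value for s, so the calculation fixes the direction of the error but not its size.

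**The case against.** The strongest reply is that self-report is not the only chance to detect an event. Korean medicine doctors see participants at up to 24 sessions, several listed events are visible there, and the coordinator monitors medical condition. The participants have MCI, not dementia: general cognition must be normal and daily activities not impaired. Most listed events are needling events, confined to the 8 treatment weeks and usually followed by another session within days. The article is also condensed. The schedule figure is not shown, and question wording or CRF items may be in the full protocol.

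Much of this stands, and it limits the point. Under-recording is probably smaller for events at the needle site during a session than for delayed or between-visit events. A reader might infer that there is no scheduled contact in the last 12 weeks. That is wrong: a week-20 assessment and its reminder call are scheduled, and the gap lies between the two visits. A reader might also cite the sentence that participants notify staff and are then compensated. It concerns an AE already judged to be caused by the trial, so it says nothing about detection.

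The reply does not remove the concern. The coordinator's monitoring is tied to adherence and is not described as asking about AEs. Nor does condensation explain the reporting rule away: the article states it, and as stated it is weak.

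**Conclusion.** The point holds as a risk. Voluntary report is the only AE ascertainment method the protocol states. The sample is memory-impaired, safety is part of the hypothesis, and no contact is described between week 8 and week 20. AE counts may be too low, in the direction of a conclusion of safety.

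The size is unknown. A reader might infer that the safety conclusion will certainly rest on an undercount, or might put assumed capture rates into the limit above. The documents support neither, because they give no basis for any capture rate. A reader might also suspect that the unblinded arms would report at different rates. Nothing in the documents shows this.

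The conclusion assumes that the full protocol and its schedule contain no active AE questioning beyond what the article describes. If they do, the article's sentence still misstates the method and should be corrected.

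**What to change.** In Occurrence of adverse events, replace the sentence on required voluntary reporting with active collection:
- The coordinator asks one fixed, non-leading AE question at each of the 24 sessions (covering the time since the last contact), at the week-8 visit and at the week-20 visit.
- An accompanying family member or guardian is asked too, where present.
- Each AE is recorded as solicited, spontaneous or staff-observed.
- The collection window is stated as first treatment to week 20.

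A telephone call partway through weeks 8 to 20 would shorten the longest recall period, but is optional.

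The cost is about one CRF line per existing visit. Recorded AE rates will be higher than under spontaneous reporting, and this should be said when they are reported. Recruitment began in February 2019, so participants already enrolled will have mixed collection methods and must be flagged. The change needs approval from the institutional review board, as Quality assurance requires for any revision. Confidentiality and data management places the coordinator outside data collection, so that sentence must be reconciled with the coordinator's role in recording AEs.

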### Study design and setting

This study is a prospective, outcome-assessor-blinded, parallel-arm, single-center (DongShin University Gwangju Korean Medicine Hospital, Republic of Korea), randomized controlled clinical trial with a 1:1:1:1 allocation ratio. A total of 32 participants, who meet the inclusion and exclusion criteria, will be randomly allocated to a basic acupuncture (BA), an acupoint specificity (AS), a needle duration (ND), or an electroacupuncture (EA) group (*n* = 8 each). The patients will receive acupuncture treatment once per day, 3 days/week for 8 weeks.

The outcome measure will be improvement in cognitive function evaluated using the Korean version of the Alzheimer’s Disease Assessment Scale—cognitive subscale (ADAS-K-cog) and the Korean version of the Montreal Cognitive Assessment (MoCA-K), and improvement in scores on the Center for Epidemiological Studies Depression (CES-D), Korean Activities of Daily Living (K-ADL), Korean Instrumental Activities of Daily Living (K-IADL), and European Quality of Life Five Dimension Five Level (EQ-5D-5L) scales. All scores will be recorded at baseline (before intervention), 8 weeks after the first intervention (i.e., at the end of the intervention period), and 12 weeks after completion of the intervention.

The design of this study, including outcomes measured and evaluation schedules, is based on the designs of several previous studies that have evaluated acupuncture treatment for cognitive impairment [11, 12, 15]. This manuscript has been written in accordance with the Standard Protocol Items: Recommendations for Interventional Trials (SPIRIT) and Consolidated Standards Of Reporting Trials (CONSORT) 2010 guidelines [16, 17] (see Additional file 1).

This study protocol complies with the principles of the Declaration of Helsinki and Korean Good Clinical Practice guidelines. The trial has been registered at http://cris.nih.go.kr (registration number: KCT 0003430; registration date: 16 January 2019). The study design is summarized in Figs. 1 and 2.

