### Dropout criteria

Participants will be dropped from the trial under the following conditions: less than 75% compliance with the protocol procedures (i.e., participating in fewer than 18 of the 24 scheduled treatment sessions); occurrence of a serious adverse event (SAE); reluctance to continue the trial; incomplete data that could influence the trial; large error in protocol or significant deviation in implementation; or if the principal investigator (PI) or institutional review board (IRB) decide to terminate their participation in the trial.

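### The SAE definition covers only disabling events or malfunction, so other grave events are recorded as AEs but need not be classed as serious or reported at once

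*Protocol article*

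**What the plan says.** The protocol article uses the SAE concept in two places and refers to safety in a third.

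- **Occurrence of adverse events.** AEs are defined broadly: "Adverse events (AEs) are undesirable and unintentional signs, symptoms, or diseases that appear during or after treatment in a clinical trial". Capture is meant to be complete: "All AEs that occur during the trial will be documented". The CRC records timing, severity, measures taken and possible causality, and passes every AE to the PI and IRB. The serious subset is then singled out: "In the case of SAEs, defined as those causing severe disability or malfunction". For that subset, "appropriate measures will be taken and the incident will be immediately reported to the PI and relevant IRB".
- **Dropout criteria.** The conditions for dropping a participant include "occurrence of a serious adverse event (SAE"). The same list ends with a discretionary route: "or if the principal investigator (PI) or institutional review board (IRB) decide to terminate their participation in the trial".
- **Hypothesis.** The null hypothesis contains the statement that "acupuncture is not safe for MCI patients". It is not linked to SAEs or to any number of events.

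**The concern.** The SAE clause is a closed definition. It does not offer disability and malfunction as examples, although the same section does use open wording when it lists possible AEs. Someone applying it as written would find that several kinds of grave event do not qualify.

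The label has consequences. It is the only thing in the article that attaches a speed to reporting, and it triggers one of the dropout criteria. It is also the only definition available to anyone who later writes how many serious events occurred. Safety is part of the stated hypothesis and participants are aged 55–85, so a sentence about serious events is likely to appear in the report. Under this definition that sentence could understate them.

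**Working it through.** The document states no SAE count, rate or threshold, so there is no planned figure to reproduce. The check is to apply the wording to different kinds of event.

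**Step 1. Which events meet the definition?**

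| Event | SAE on the literal wording? | Documented and reported as an AE? | Immediate report required? | SAE dropout criterion met? |
|---|---|---|---|---|
| Event leaving severe disability | Yes | Yes | Yes | Yes |
| Life-threatening event that resolves | No | Yes | No | No |
| Hospital admission without severe disability | No | Yes | No | No |
| Death | Open to reading | Yes (the event or the illness behind it) | Open to reading | Not a practical question |

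Death is not named. A reader could stretch malfunction to cover it, but could equally decline to. The two middle rows are the clear cases.

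**Step 2. What is lost for the middle rows?** Three things: the serious classification, the required speed of reporting, and the automatic SAE dropout trigger. The record itself is not lost, nor the severity and causality assessment, nor the report to the PI and IRB, for which no time is stated. The PI or IRB can still end participation by decision.

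**Step 3. Does another rule supply the speed?** No. Under Participant recruitment, the CRC is to monitor participants' medical condition continuously, which helps detection but sets no reporting time. Under Quality assurance, the DMC's stated task is the validity of the data. The SAE clause is the only time-critical route described.

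**Step 4. How many events might be concerned?** This is an illustration only.

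- Participants: 32 (Sample size estimation).
- Follow-up: 8 weeks of treatment + 12 weeks afterwards = 20 weeks (Study design and setting; Statistical analysis).
- Exposure with complete follow-up: 32 × 20/52 = 12.3 person-years.
- Yearly rate of hospital admission or death: 5–20%. This is an assumption; the document gives no rate.
- Expected events: 12.3 × 0.05 = 0.6, to 12.3 × 0.20 = 2.5.

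This range is an upper figure for the events at issue, because some would also cause severe disability and so already count as SAEs. The Exclusion criteria remove people with cancer or serious cardiovascular, cerebrovascular, liver or kidney disease, which points towards the lower end.

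**Step 5. What does the planned analysis use?** The outcomes listed are all scale scores, and Statistical analysis describes no safety analysis. The figure of 32 was set by funding, the single centre and time. None of these depends on the SAE definition.

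**The case against.** The strongest reply has four parts.

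1. **Nothing disappears from the safety data.** A reader might infer that grave events without disability would go unrecorded. The text does not support that: AE capture is broad, severity and causality are recorded, and all AEs reach the PI and IRB. This part stands in full, and the point is limited to classification and speed.

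2. **No safety result depends on an SAE count.** A reader might infer that the trial's safety conclusion rests on such a count. No section specifies one, and the safety part of the hypothesis is not tied to SAEs. This also stands. What remains is that any SAE statement the authors choose to make would use the only definition given.

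3. **The article is a short form.** Trial status names a separate protocol (version 1.1), Quality assurance refers to standard operating procedures, and Study design and setting says the protocol "complies with the principles of the Declaration of Helsinki and Korean Good Clinical Practice guidelines". A fuller working definition may exist there. This limits what can be claimed about practice at the site. It does not remove the point, because the article states a definition rather than leaving one out. The content of the guidelines is not in the document, so no conflict with them is asserted.

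4. **A wider definition has a side effect.** Because an SAE is a dropout criterion, more SAEs would mean more removals, possibly for admissions unrelated to acupuncture. This stands and must be dealt with in the fix.

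The discretionary power of the PI or IRB to end participation is a partial safeguard. It does not set a reporting time, and it does not classify the event.

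**Conclusion.** The point holds in a limited form. As written, the SAE definition excludes life-threatening events that resolve and hospital admissions without severe disability; whether it excludes death is open to reading. Such events are recorded and reported as AEs, but they need not be classed as serious or reported immediately, and a statement about serious events could understate them.

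The size is modest: about 0.6 to 2.5 admissions or deaths over 12.3 person-years, on assumed yearly rates of 5–20% and complete follow-up. The conclusion does not depend on those rates, because it follows from the wording. Sample size, power and the efficacy analyses are unaffected. It is worth correcting because the defect is in a stated rule that governs urgent safety reporting, and the correction is small.

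**What to change.** In Occurrence of adverse events, extend the SAE definition so that it names death, threat to life and hospitalisation alongside disability. Apply the immediate-reporting rule, and any reporting of SAEs in the results, to that definition. If the full protocol already contains a wider definition, bring the article's sentence into line with it.

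The cost is one sentence in the protocol, the matching CRF entry, and the IRB approval that Quality assurance requires for revisions. More events will be classed as SAEs.

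There is one further consequence. The Dropout criteria use the same term, so the wider definition would also widen removal from the trial. On the illustrative range, that is at most 0.6 to 2.5 of 32 participants (0.6/32 = 2% to 2.5/32 = 8%), in arms of 8. The sponsor must reconcile the two sections and decide what the dropout rule should be; this review takes no position on that rule.
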